# **Data Management**

## *7.1. Data collection*

A single person (registered dietitian) will be responsible for data input. The patients will be identified by a registration number and will remain anonymous. Data will be progressively (after each evaluation) collected in a locked electronic database (Microsoft Office EXCEL). At the end of the study, data will be verified for accuracy and completeness.

## *7.2. Database management and quality control*

After the last evaluation of the last patient, the database will be checked for data quality and plausibility. This will be completed with the treatment codes (*Treatment A* or *Treatment B*), which will be masked during the statistical analysis (database closed).

# **Statistics and sample size**

***8.1 Sample size***

In the absence of preliminary data to estimate the expected treatment difference, the sample size was set at 128 patients reaching the evaluation of the primary endpoint (64 per arm) to achieve a statistical power of 80% (type I error 5% using a two-tailed test) to detect a clinically meaningful difference (mean treatment difference/standard deviation [effect size]=0.5). Allowing for a 10% drop-out rate in each arm, it was decided to randomize 140 patients (70 per treatment arm).

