# **Study design**

A single-site, interventional, randomized (1:1), parallel-group, double-blind, controlled, 8-week clinical trial.

Expected study duration: 24 months.

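### Section 8.1: randomising 140 patients with 10% dropout leaves 126 evaluable, not the required 128; the real allowance is 12 losses (8.6%), and the effect on power is marginal

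*Protocol*

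**What the plan says.** Section 8.1 of the protocol gives every input of the sample size.

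- Evaluable patients: "the sample size was set at 128 patients reaching the evaluation of the primary endpoint (64 per arm").
- Target: 80% power, with "type I error 5% using a two-tailed test".
- Effect: "mean treatment difference/standard deviation [effect size]=0.5", chosen without preliminary data.
- Dropout and number randomised: "Allowing for a 10% drop-out rate in each arm, it was decided to randomize 140 patients (70 per treatment arm").

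The Study design section confirms 1:1 allocation. Section 8.2 restricts the efficacy population to patients who reach the primary endpoint assessment. Patients who drop out come back only in a supportive sensitivity analysis that assigns them the worst outcome.

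**The concern.** The 128 is defined as a number after dropout and the 140 as a number before it, so the stated dropout rate should lead from one to the other. It does not. A reader who takes the paragraph at face value will believe that 14 losses among 140 still leave 128 patients for the primary analysis, when they leave 126.

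The sample size paragraph is the design's quantitative justification, and readers will recheck it. At stake is whether the plan delivers the evaluable number it sets for itself under its own dropout assumption.

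**Working it through.** **Inputs**, all from section 8.1 except the allocation (Study design): two-sided alpha 0.05; power 80%; standardised difference d = 0.5; 64 evaluable per arm; dropout 10% in each arm; 70 randomised per arm; allocation 1:1.

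**Step 1. Reproduce the evaluable number.**

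- Normal approximation: n per arm = 2(1.960 + 0.842)² / 0.5² = 62.8, rounded up to 63.
- Two-sample t test (noncentral t): the exact requirement is 63.8, rounded up to 64 per arm, with power 80.15%.

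The stated 64 per arm (128) is therefore reproduced by the t test and not by the normal approximation.

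**Step 2. Apply the stated dropout to the stated number randomised.**

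- Per arm: 70 × 0.90 = 63, against 64 required.
- In total: 140 × 0.90 = 126, against 128 required.

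**Step 3. Find the dropout that 140 does allow.**

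- 140 − 128 = 12 losses, and 12/140 = 8.6% (6 of 70 in each arm).

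**Step 4. See whether any usual inflation of 128 gives 140.**

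| Rule | Per arm | Total |
|---|---|---|
| Divide by 0.90 | 64/0.90 = 71.1, so 72 | 128/0.90 = 142.2, so 143 (144 with equal arms) |
| Multiply by 1.10 | 64 × 1.10 = 70.4 | 128 × 1.10 = 140.8 |

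Dividing is the correct rule and needs 3 to 4 more patients than stated. Multiplying comes close to 140, but only after rounding a minimum downwards. The figure 126/0.90 = 140 is an exact match, and 126 is the normal-approximation total (2 × 63), but it is not the number the protocol says it needs.

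**Step 5. Size of the effect on power** (d = 0.5, two-sided 5%).

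Normal approximation: power = Φ(d√(n/2) − 1.960). For n = 63 this is Φ(2.806 − 1.960) = Φ(0.846) = 80.1%. For n = 64 it is Φ(2.828 − 1.960) = Φ(0.868) = 80.7%. The t-test figures use the noncentral t with the same noncentrality (2.806 and 2.828) and 2n − 2 degrees of freedom.

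| Evaluable per arm | t test | Normal approximation |
|---|---|---|
| 63 | 79.5% | 80.1% |
| 64 | 80.1% | 80.7% |

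The loss is about 0.6 percentage points by either method.

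**The case against.** The strongest reply is that this is a rounding matter with no practical consequence. Much of that stands.

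- Power is stated as a whole number, and 79.5% rounds to 80%. By the normal approximation 63 per arm still exceeds 80%.
- Section 8.1 names no test, and section 8.2 plans a regression model with robust standard errors, so the t test used here is an assumption. It is a reasonable one, because it is the method that gives 64 per arm.
- The effect size was set without preliminary data and the 10% is a round guess. The effect detectable with 80% power by the t test is 0.503 with 63 per arm and 0.499 with 64. No design decision turns on that difference.
- The likely origin is benign: 10% was added to 64 and the result rounded to 70.

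What does not stand is that the figures are therefore consistent. The three whole numbers sit in one paragraph, the 128 is explicitly a count after dropout, and section 8.2 leaves dropouts out of the primary analysis. The worst-outcome analysis retains them but is only supportive. Tolerance for rounding can excuse a computed figure; it does not turn 126 into 128.

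A reader might go further and infer that the trial fails to deliver its 80% power, or that it sits exactly at 80% with nothing to spare. The documents do not support either reading. Whether 63 per arm falls below 80% depends on the formula, and the gap is at most half a percentage point. With 64 per arm there is a margin, though a very small one: power is 80.15% and the exact requirement is 63.8.

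**Conclusion.** The inconsistency is real and minor. With 140 randomised and 10% dropout in each arm, section 8.1 yields 126 evaluable patients, two fewer than the 128 it requires. The design allows for 12 losses (8.6%), not 14 (10%).

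The arithmetic rests on the protocol's own figures alone. The power statement also assumes d = 0.5, equal arms after dropout and a two-sample comparison of means. What is wrong is the evaluable number and the dropout allowance. The paragraph gives no ground for calling the trial underpowered or for requiring a larger enrolment.

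**What to change.** Change one sentence in section 8.1, in one of two ways:

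- keep 128 evaluable and state that randomising 140 patients allows for 12 dropouts (8.6%); or
- keep the 10% and state that 140 patients then leave 126 evaluable (63 per arm), giving about 79.5% power for an effect size of 0.5.

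Neither version changes enrolment, procedures or the analysis. The only cost is that the stated allowance, or the stated power, becomes slightly less favourable. Holding both 128 and 10% would take 143 randomised, or 144 with equal arms; a gain of about 0.6 points in power does not call for that.

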***8.2 Statistical analysis***

The efficacy analysis population will include the patients reaching the primary endpoint evaluation and it will be performed according to the intention to treat principle.

All patients consuming at least one serving of nutritional formula will be included in the safety analysis.

Descriptive statistics: Mean and standard deviation, range, median and quartiles will be calculated for continuous variables. Frequencies and percentages will be calculated for categorical variables.

Analysis of study endpoints: Expecting a treatment effect also on the LOS, changes over time in both primary and secondary continuous outcome variables will be normalized by the duration of observation in months. Changes will be calculated so that an improvement would result in a positive value in favor of the experimental formula (as either final - initial value or initial - final values).

*Primary endpoint* - The change in gait speed will be compared between groups with a generalized linear regression model using Huber-White robust standard errors to account for variance inhomogeneity. Then a series of supportive analyses of the primary endpoint will be performed. First, we will conduct a multivariable model, to adjust for potential confounders regardless of differences in baseline features, including gender, age and monthly change in energy intake, creatinine and in total cholesterol. Second, a conservative sensitivity analysis of the primary endpoint using the worst possible outcome of the study for patients dropping out will be performed.

*Secondary endpoints* - Group comparison will be performed for all secondary endpoints on a continuous scale using an unadjusted generalized linear regression model. For both primary and secondary outcome variables the mean change within groups will be also assessed. For secondary endpoints on a binomial scale, a generalized linear model for the binomial family will be used. For all endpoints the treatment effect (mean or frequency difference) and 95% confidence interval (CI) will be reported.

All statistical analyses will be performed using the software STATA 15.0 statistical software (Stata Corporation, College Station, TX).

Dropout

The following causes of dropout will be considered:

- Death

- Lost to follow-up (due to hospitalization or transfer to another setting of care)

- Withdrawal

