***2.2 Secondary endpoints***

The following key secondary endpoints (change per month in physical performance outcome measures) will be investigated:

- chair-stand test
- Timed up and go (TUG) test
- Short Physical Performance Battery (SPPB)

The following secondary endpoints will be also addressed:

- change per month in handgrip strength
- change per month in Tinetti scale
- change per month in Barthel Index
- change per month in activities of daily living (ADL) score
- change per month in body weight
- change per month in appendicular muscle mass (AMM)
- change per month in skeletal muscle mass index (SMMI)
- change per month in cognitive status (Trail making test and Mini Mental State Examination [MMSE])
- change per month in quality of life (Short-Form 12-Item Health Survey [SF-12])
- the proportion of patients who improved their rehabilitation intensity profile
- the modality of discharge (home vs. institution)
- the overall economic benefits (using length of stay [LOS] and total duration of rehabilitation [minutes] as surrogate measures)
- safety of the intervention

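### The efficacy population is available-case but is called intention to treat, and only the primary endpoint has an analysis that brings dropouts back

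*Protocol*

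**What the plan says.** Protocol section 8.2 defines the population for efficacy and names its principle in one sentence: the "efficacy analysis population will include the patients reaching the primary endpoint evaluation and it will be performed according to the intention to treat principle". Section 8.1 shows that the restriction is deliberate, since "the sample size was set at 128 patients reaching the evaluation of the primary endpoint (64 per arm"), while 140 are randomised to allow for 10% dropout per arm.

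Under its Dropout heading, section 8.2 lists death, withdrawal, and "Lost to follow-up (due to hospitalization or transfer to another setting of care"). The assessment table under Methods has only two time points, baseline and end of study, so a patient who leaves early has no later gait-speed value.

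For the primary endpoint, section 8.2 adds a supportive sensitivity analysis that gives dropouts the worst outcome seen in the study. It states no counterpart for the secondary endpoints. One of these, in section 2.2, is "the modality of discharge (home vs. institution"), to be analysed with a binomial generalized linear model.

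**The concern.** An intention-to-treat analysis keeps every randomised patient in the allocated arm. A population limited to those with the end-of-study measurement does not, so the headline comparison would carry a name that its definition does not support. The protocol itself fixes this population, so it is not a detail left to a statistical analysis plan.

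The label matters because several reasons for leaving may be related to outcome. Death and hospitalisation are unfavourable events in older rehabilitation patients. If such losses differ between arms, in number or in prognosis, the comparison of evaluated patients is no longer protected by randomisation.

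Modality of discharge is the least protected endpoint. Patients who die, are hospitalised or are transferred before the evaluation fall outside the stated population, although where they went is often known. Transfer to another care setting also overlaps with what the endpoint measures.

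**Working it through.** **1. The plan's own figures (section 8.1).** Inputs: effect size 0.5 ("mean treatment difference/standard deviation [effect size]=0.5"), power 80%, and "type I error 5% using a two-tailed test". A two-sample t-test needs 63.77, so 64 per arm and 128 in total, which matches the protocol; power at 64 per arm is 80.1%. The normal approximation gives 63 per arm.

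Patients outside the efficacy population:
- at 10% dropout, 0.10 × 140 = 14, leaving 126 (power 79.5%);
- taking the 128 target literally, 140 − 128 = 12.

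The shortfall of 2 against 128 is immaterial. The point is that about 14 randomised patients are expected to be missing from an analysis called intention to treat.

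**2. Bias in a mean difference.** Let m be the mean change among evaluated patients in an arm, d the dropout proportion, and D the amount by which dropouts' true change lies below m. The all-randomised mean in that arm is (1 − d)m + d(m − D) = m − dD. With the same D in both arms:

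evaluated-only difference − all-randomised difference = (d_exp − d_ctl) × D.

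The protocol assumes 10% in each arm and gives no value for D. The uneven split and the values of D below are therefore assumptions; the split averages to the planned 10%.

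| Dropout, experimental vs control | D = 0.5 SD | D = 1 SD | D = 2 SD |
| --- | --- | --- | --- |
| 10% vs 10% | 0 | 0 | 0 |
| 15% vs 5% | +0.05 | +0.10 | +0.20 |
| 5% vs 15% | −0.05 | −0.10 | −0.20 |

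Against the design effect of 0.5 SD, these non-zero values are 10%, 20% and 40%, in either direction.

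**3. Modality of discharge.** Assume 9 experimental and 5 control patients lost (14 in all, the planned number), the same home rate h among evaluated patients in both arms, and lost patients counted as not discharged home. Evaluated patients number 70 − 9 = 61 and 70 − 5 = 65.

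- Evaluated-only difference: h − h = 0.
- All-randomised difference in size: h × (65 − 61)/70 = h × 4/70.
- h = 60%: 0.6 × 4/70 = 3.4 points. h = 90%: 0.9 × 4/70 = 5.1 points.

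**4. How far the planned worst-outcome analysis helps.** Simulation with 70 per arm, 4,000 runs, normal outcomes, a Welch test, a true effect of 0.5 SD among evaluated patients, and dropouts given the worst observed value:

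| Dropouts, experimental vs control | Evaluated-only estimate | Worst-outcome estimate | Proportion significant, evaluated-only → worst-outcome |
| --- | --- | --- | --- |
| 7 vs 7 | 0.50 | 0.45 | 80% → 59% |
| 10 vs 4 | 0.50 | 0.22 | 78% → 11% |
| 4 vs 10 | 0.50 | 0.68 | 79% → 95% |

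The analysis does bring dropouts back and would show dependence on them. It is not always conservative: when more control patients drop out, it favours the experimental formula.

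**The case against.** The strongest reply is that the primary endpoint already has an analysis including every dropout, and that section 8.1 expects equal dropout, for which the formula gives no bias when the outcome gap is also equal. Both points stand. They limit the likely harm to gait speed, but the worst-outcome analysis is supportive only and the label on the main result remains wrong.

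A reader might infer that efficacy is assessed only in patients who did well. The documents do not support this. Section 5.1 ends the programme on a plateau or at 8 weeks, so patients who hardly improve are still evaluated. Withdrawal is also a listed cause, and neither withdrawal nor transfer need be a bad outcome.

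A reader might likewise infer that the discharge endpoint removes its own failures. It does not remove the ordinary ones: a patient who finishes rehabilitation and goes to an institution has the end-of-study visit, where modality of discharge is recorded. Only those lost before that visit are affected. Taking the shift in the 9 vs 5 example as the full 4/70 = 5.7 points would also go too far, since it holds only if every evaluated patient goes home.

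Extending the point to length of stay is tempting too, but the protocol says nothing on how early losses count there, and a statistical analysis plan may settle it.

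Finally, multiple imputation is not a cure. With one post-baseline assessment it relies on baseline variables, so it cannot remove dropout that depends on the unseen outcome, and a gait speed after death has no clear meaning.

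**Conclusion.** The concern holds for the label and for the lack of stated protection of modality of discharge. Section 8.2 calls an available-case population intention to treat, and the protocol's own numbers put about 14 of 140 randomised patients outside it. This follows from the text and needs no assumption.

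The size of any bias does rest on assumptions. It is zero if dropout and outcome gap are equal across arms. It is 0.05 to 0.20 SD in either direction under the assumed 5% vs 15% dropout and gap of 0.5 to 2 SD. For discharge it is about 3.4 to 5.1 percentage points for an assumed 9 vs 5 lost. The documents do not show that dropout will differ by arm, nor which arm would benefit.

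**What to change.** In section 8.2:

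1. Define the intention-to-treat population as all 140 randomised patients, analysed as allocated. Rename the present population available-case wherever it is used, and do not describe its results as intention to treat.
2. Analyse modality of discharge in all randomised patients using the known destination. Count those who died, were hospitalised or were transferred before the evaluation as not discharged home, and report the endpoint as discharged home vs. not. This makes it a composite, so the new name should be used throughout.
3. For gait speed, report an all-randomised analysis beside the available-case result: the worst-outcome analysis already planned, and multiple imputation as a further sensitivity analysis with deaths handled separately.

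The cost is rewording and a little more analysis, with no new patients or visits. The estimate may become slightly less favourable.

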***2.1 Primary endpoint***

The primary endpoint will be the mean change in gait speed per month (m/s/month) during the 4-meter walking test.

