***5.2 Nutritional intervention***

An individualized dietary program will be drawn up for each patient, taking nutritional and mastication issues, as well as any swallowing issues into consideration. In addition to hospital diet, subjects will be randomly allocated to receive twice daily:

a) Experimental formula: a whey protein-based food for special medical purposes enriched with leucine and vitamin D (Fortifit®, Nutricia). Each serving consists of 40 g of powder (vanilla or strawberry flavor), providing 150 kilocalories and containing 20 g of whey proteins, 2.8 g of leucine, 9 g of carbohydrates, 3 g of fat, 800 IU of vitamin D, and a mixture of vitamins, minerals (calcium, 500 mg), and fibers [17-20].

b) Control formula: an isocaloric formula consisting of 40 g of a flavored (vanilla or strawberry) powder containing maltodextrins.

The intervention formula will be reconstituted with 100-150 mL water and administered at breakfast and in the afternoon. In the event of dysphagia to liquids, the density of the reconstituted formula will be increased, as appropriate.

The actual supplement and control formula will be given in identical containers devoid of any labelling for at least 4 weeks (minimum duration of the rehabilitation) up to 8 weeks (maximum duration of the rehabilitation). Compliance with intake of nutritional interventions will be monitored by recording the number of servings consumed every day in a diary.

1. **Methods**

The assessments and the procedures to be performed throughout the study are summarized in the following table:

| ASSESSMENTS/PROCEDURES | BASELINE | END OF STUDY |
| --- | --- | --- |
| Inclusion/exclusion criteria | X |  |
| Informed consent | X |  |
| Medical history & demographics | X |  |
| Randomization | X |  |
| Anthropometry | X | X |
| Protein-calorie intake | X | X |
| Mini Nutritional Assessment | X | X |
| Physical performance | X | X |
| Physical function | X | X |
| Muscle strength (handgrip) | X | X |
| Muscle mass | X | X |
| Cognitive function | X | X |
| Biochemistry | X | X |
| Quality of life | X | X |
| Complexity of assistance needs | X | X |
| Compliance to nutritional intervention |  | X |
| Safety data |  | X |
| Modality of discharge |  | X |
| Total duration of rehabilitation |  | X |
| Length of stay |  | X |

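### Section 8.2 does not name the endpoint's baseline value as a covariate in any comparison of change, so the change score corrects baseline only with a fixed slope of 1 and may give up precision

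*Protocol*

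**What the plan says.** Protocol section 2.1 defines the endpoint: "The primary endpoint will be the mean change in gait speed per month (m/s/month) during the 4-meter walking test". Section 8.2 extends the same scaling to the other outcomes: "changes over time in both primary and secondary continuous outcome variables will be normalized by the duration of observation in months". Each change is a simple difference between the final and initial values, signed so that improvement is positive.

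For the primary comparison, section 8.2 states: "The change in gait speed will be compared between groups with a generalized linear regression model using Huber-White robust standard errors". It names no covariate there. Adjustment comes afterwards, in a supportive multivariable model with covariates "including gender, age and monthly change in energy intake, creatinine and in total cholesterol". Baseline gait speed is not among them. For the secondary endpoints the wording is explicit: "Group comparison will be performed for all secondary endpoints on a continuous scale using an unadjusted generalized linear regression model".

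The baseline values exist. In the assessment schedule under Methods, the row "Physical performance | X | X" marks physical performance at both baseline and end of study. Function, handgrip, muscle mass, cognition, quality of life and anthropometry are marked the same way. Length of stay and total duration of rehabilitation are marked at end of study only.

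**The concern.** A change score takes out the baseline by subtraction, that is, with a coefficient fixed at 1. This is the best linear correction only if the regression slope of follow-up on baseline is 1. If the slope is below 1, change is negatively correlated with baseline: patients who start low tend to gain more, partly through regression to the mean. That is plausible here. Gait speed is one of the sarcopenia criteria for entry (section 4.1), and several secondary scales are bounded (SPPB 0 to 12, Barthel Index 0 to 100, Tinetti up to 40).

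Two things are then at stake. The residual variance is larger than it need be. And if the arms happen to differ at baseline, part of that difference stays in the estimated treatment effect. Section 8.1 says the trial was sized without preliminary data, so precision that costs no extra patients is worth having.

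**Working it through.** **Inputs from the protocol.** Section 8.1 sizes the trial "to achieve a statistical power of 80% (type I error 5% using a two-tailed test") with "mean treatment difference/standard deviation [effect size]=0.5", at 64 evaluable patients per arm. Section 3 gives 1:1 allocation. The protocol gives no correlation r between baseline and follow-up, no standard deviations, and no relation between baseline and length of stay. All values for these below are assumptions.

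**1. The plan's own figure.** A two-sample t-test with effect size 0.5, two-sided 5% and 64 per arm (126 degrees of freedom) has 80.1% power. The planned 128 evaluable patients are reproduced.

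**2. Gain with equal variances at both visits.** With common variance s²:

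- variance of the change: 2(1 − r)s²
- residual variance after adjusting for baseline: (1 − r²)s²
- ratio: (1 − r²) / [2(1 − r)] = (1 + r)/2

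The effective effect size becomes 0.5/√ratio, with 125 degrees of freedom:

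| r (assumed) | variance ratio | power at 64 per arm |
| --- | --- | --- |
| none (unadjusted) | 1.00 | 80.1% |
| 0.5 | 0.75 | 90.0% |
| 0.6 | 0.80 | 88.1% |
| 0.7 | 0.85 | 86.1% |
| 0.8 | 0.90 | 84.1% |

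Expressed as patients, 128 × 0.75 = 96 and 128 × 0.90 = 115. At these correlations the unadjusted analysis therefore costs the equivalent of about 32 to 13 of the 128.

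**3. The per-month scale.** The formula above is for an undivided change, whereas the endpoint is divided by months of observation.

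- *Duration unrelated to baseline.* A simulation (duration uniform over 28 to 56 days, Huber-White-type standard errors, 3,000 runs) gave 79.8%, 78.8% and 79.9% power unadjusted. With baseline added it gave 88.7%, 84.2% and 83.7%, at r = 0.5, 0.7 and 0.8. This is close to the table.
- *Slower patients stay longer.* Dividing by a longer stay weakens the negative correlation. With r = 0.8, a mean gain of 1 SD and a baseline-to-duration correlation of −0.3 to −0.5, the ratio is 0.95 to 0.97 and power is 82.1% to 81.3%.
- *Overall.* With the same mean gain of 1 SD, r from 0.5 to 0.8 and that correlation from 0 to −0.5, the ratio runs from 0.77 to 0.97.

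**4. Unequal variances.** If the follow-up SD is k times the baseline SD (undivided change), the slope is rk and the ratio is k²(1 − r²)/(1 + k² − 2rk).

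- k = 1.2, r = 0.5: 1.44 × 0.75 / 1.24 = 0.87, power 85.2%
- k = 1.2, r = 0.8: 1.44 × 0.36 / 0.52 = 0.997, power 80.3%
- k = 1.25, r = 0.8: the slope is 1, the ratio is 1.00 and the gain is nil

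**5. Chance imbalance.** With 64 per arm, the baseline difference between arms has SD √(2/64) = 0.18 baseline SD, with a 95% range of about ±0.35. A difference above 0.2 SD in either direction has probability of about 26%. If change and baseline correlate at −0.3 to −0.5, a 0.2 SD imbalance shifts the unadjusted estimate by 0.06 to 0.10 SD of change. Against the target of 0.5, that is 12% to 20%.

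**The case against.** The strongest reply is that nothing here is invalid. Under 1:1 randomisation the difference in mean change is unbiased on average and keeps its type I error. It also matches the sample size, which is a plain two-sample calculation reaching its 80%. All of that stands.

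A reader might infer that the plan disregards baseline altogether, or that its estimate is biased. The protocol does not support either reading. Section 8.2 subtracts the initial value from every change outcome, so baseline is corrected, though with a fixed slope. The shift in step 5 is conditional on an imbalance that may not occur: about three times in four the difference will be under 0.2 SD.

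A reader might also take 90% power as the expected gain. That fails too. The figure needs r = 0.5 and equal variances, and the protocol supports neither. Selecting patients on gait speed can itself narrow the baseline spread relative to follow-up, which moves the slope towards 1 and reduces the gain. A link between slow gait and a long stay does so as well.

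The covariate list of the supportive model opens with a word that may leave it incomplete, so baseline gait speed is not strictly excluded there. That does not change the primary model, which names no covariate, or the secondary models, which are expressly unadjusted.

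**Conclusion.** The point holds as a recommendation on efficiency and on balance conditional on the observed baseline. It is not an error of validity. The protocol fixes analyses of change that do not use the collected baseline as a covariate.

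For the primary endpoint at 64 per arm, the gain from adding it ranges from nil to about 10 percentage points of power. The upper end assumes equal variances and r = 0.5. The lower end arises when the slope of follow-up on baseline is near 1. The reading of the primary model as unadjusted rests on the absence of any named covariate and on the contrast with the later multivariable model; for the secondary endpoints it is stated outright.

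**What to change.** In section 8.2:

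- Define the primary model as a regression of monthly change in gait speed on arm and baseline gait speed, keeping the Huber-White standard errors.
- For each continuous secondary endpoint expressed as a change per month, add that endpoint's own baseline value as a covariate. Exclude length of stay and total rehabilitation minutes, which have no baseline.
- Report the unadjusted differences as supportive.

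The change should be made before the treatment codes are linked to the data, so that the choice between adjusted and unadjusted estimates cannot depend on the results.

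The cost is a short edit to 8.2 and one degree of freedom per model (125 instead of 126 for the primary at 128 patients). If baseline turned out to be uncorrelated with change, power would stay at 80.1%. No new data are needed, and the sample size does not have to change.
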